## Abstract

**Background:**

Some studies have suggested that the early sustained lung inflation (SLI) procedure is effective in decreasing the need for mechanical ventilation (MV) and improving respiratory outcome in preterm infants. We planned the present randomized controlled trial to confirm or refute these findings.

**Methods/Design:**

In this study, 276 infants born at 25^+0^ to 28^+6^ weeks’ gestation at high risk of respiratory distress syndrome (RDS) will be randomized to receive the SLI maneuver (25 cmH_2_O for 15 seconds) followed by nasal continuous positive airway pressure (NCPAP) or NCPAP alone in the delivery room. SLI and NCPAP will be delivered using a neonatal mask and a T-piece ventilator.

The primary endpoint is the need for MV in the first 72 hours of life. The secondary endpoints include the need and duration of respiratory support (NCPAP, MV and surfactant), and the occurrence of bronchopulmonary dysplasia (BPD).

**Trial registration:**

Trial registration number:
NCT01440868

## Background

The pathogenesis of bronchopulmonary dysplasia (BPD) in preterm infants is multifactorial, but the role of ventilator-induced lung injury (VILI) is very important [1]. Although the respiratory support of preterm infants with respiratory distress syndrome (RDS) has improved and new modes of mechanical ventilation (MV) have been developed, the occurrence of BPD has remained substantially unchanged. Nevertheless, one aspect of respiratory care in preterm infants which has not yet been thoroughly investigated is respiratory assistance in the delivery room immediately after birth. In fact, lung protection should start in the delivery room where, from the first breaths, the preterm infant can be helped to clear the lung fluid; to recruit alveolar spaces facilitating the formation of the functional residual capacity (FRC); to protect the lung by avoiding large tidal volume; to avoid the continuous ‘opening and closing’ of the alveoli by delivering positive end-expiratory pressure (PEEP); and to verify the need for surfactant replacement [2,3].

Recently, some studies have investigated the effectiveness of the early sustained lung inflation (SLI) procedure in preterm infants for prevention of MV. This strategy would permit lung recruitment immediately after birth through delivery of brief peak pressure to the infant airways via a nasopharyngeal tube or mask allowing preterm infants to achieve FRC. To avoid lung collapse at the end of the expiration, the effect of PEEP is crucial. SLI and PEEP seem to have an additive effect on adequate FRC formation by permitting optimal gas exchange, improving lung mechanics and reducing the need for respiratory support.

This technique has been proven to be more effective than intermittent mandatory ventilation (IMV) in improving FRC in the asphyxiated term newborn [4,5]. Lindner *et al*. treated preterm infants by using SLI in the delivery room without a significant decrease in the MV rate or adverse effects in comparison with treatment with nasal-intermittent mandatory ventilation (NIMV) noted [6]. On the other hand, te Pas *et al*. treated preterm infants with repeatable SLI maneuvers and found a decrease in the need for MV at 72 hours of life and BPD in comparison with treatment in the delivery room with a self-inflating bag [7]. These results are in agreement with the findings of a recent paper from the same group, which demonstrates the synergistic effect of SLI and following subsequent treatment with PEEP (delivered by nasal continuous airway pressure (NCPAP)) in achieving and maintaining a FRC improvement in an animal model [8]. Moreover, Lista*et al*. recently reported that SLI followed by the delivery of NCPAP is effective in reducing the need for MV and the occurrence of bronchopulmonary dysplasia in survivors compared to NCPAP alone [9].

We therefore intend to compare the application of SLI followed by NCPAP with NCPAP alone in the delivery room to evaluate its effectiveness in decreasing the need for MV and improving respiratory outcome in preterm infants at risk for RDS.

## Methods/Design

### Aims

The primary aim of this study is to compare the need for MV in the first 72 hours of life (excluding the transient tracheal intubation performed for surfactant administration) in infants born at 25^+0^ to 28^+6^ weeks’ gestation who received the SLI maneuver in the delivery room or not.

### Study design

This will be an unblinded multicenter randomized trial of SLI versus noSLI in infants born at 25^+0^ to 28^+6^ weeks’ gestation.

### Inclusion criteria

Inborn infants satisfying the following inclusion criteria will be eligible to participate in the study:

1. Born at 25^+0^ to 28^+6^ weeks’ gestation (and)

2. High risk of RDS (and)

3. Parental consent has been obtained.

### Exclusion criteria

1. Presence of major congenital malformations.

2. Fetal hydrops.

3. Inherited disorders of metabolism.

### Primary outcome measure

The primary endpoint of this study will be the need for MV within the first 72 hours of life. Therefore, we will consider SLI a success if MV is not required and a failure if the infant needs MV. The need for MV is defined later under ‘Criteria for starting MV’.

We have chosen the need for MV during the first 72 hours of life as our primary outcome measure to maintain similarity with the main previous trial conducted on this issue [7].

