### SLI maneuver

Infants in the SLI group will undergo the following approach. After oropharyngeal and nasal suctioning, pre-ssure-controlled (25 cmH_2_O) inflation will be sustained for 15 seconds, using a neonatal mask and a T-piece ventilator, followed by the delivery of 5 cmH_2_O NCPAP. Patients will be observed for the following 6 to 10 seconds to evaluate their cardio-respiratory function. If respiratory failure persists (that is, apnea and gasping) and/or the heart rate is >60 and <100 bpm despite NCPAP, the SLI maneuver (again 25 cmH_2_O for 15 seconds) will be repeated. If the heart rate remains >60 and <100 bpm after the second SLI maneuver, the infant will be resuscitated following the current guidelines of the American Academy of Pediatrics (AAP) [17]. Moreover, if the heart rate remains <60 bpm the infant will be resuscitated following the current guidelines of the AAP [17], and a second SLI maneuver will be repeated when the heart rate increases to >60 and <100 bpm. Infants in the control group will be treated with delivery of 5 cmH_2_O NCPAP and will be assisted following the guidelines of the AAP [18].

All enrolled infants will be transferred to the NICU in NCPAP (PEEP at 5 cmH_2_O).

Neonatal care will be started with FiO_2_ of 0.21 to 0.40 in both the groups, in agreement with the local protocols. Respiratory support in the delivery room will be given using the same T-piece ventilator (Neopuff Infant T-Piece Resuscitator, Fisher & Paykel, Auckland, New Zealand), which is a pressure-limited mechanical device that supplies consistent peak inspiratory pressure (PIP) and PEEP, and is capable of delivering sustained inflation [7]. To avoid pressure leakage, a neonatal mask of appropriate size which adequately covers both the mouth and nostrils of infants will be used. The flow rate will be set at 8 to 10 l/min without changes during the resuscitation.

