### Criteria for starting MV

In the delivery room, infants will be started on MV if they have not reached the goal of 70% SpO_2_ by 5 minutes [19] and 85% by 10 minutes of life [17] with a heart rate >100 bpm, despite NCPAP at 5 cmH_2_O. In the NICU, infants will be started on MV when the pH is <7.20 with PaCO_2_>65 mmHg, PaO_2_<50 mmHg with FiO_2_ ≥0.50 after surfactant treatment, or if infants have frequent episodes of apnea (>4 episodes in 1 hour or >2 episodes requiring bag-and-mask ventilation), despite adequate NCPAP (5 to 7 cmH_2_O) delivery and oxygenation. MV will be set to maintain a PaCO_2_ of 55 to 65 mmHg and 88 to 95% SpO_2_.

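### The primary endpoint rule scores as a success an infant who dies within 72 hours without receiving MV and without meeting an MV start criterion

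*Protocol article*

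**What the plan says.** All references are to the protocol article.

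- **Primary outcome measure.** "The primary endpoint of this study will be the need for MV within the first 72 hours of life". The scoring rule follows: "Therefore, we will consider SLI a success if MV is not required and a failure if the infant needs MV". The section then points elsewhere for the definition: "The need for MV is defined later under" the section on criteria for starting MV. The reason given for the endpoint is similarity with the main previous trial.
- **Criteria for starting MV.** For the delivery room: "In the delivery room, infants will be started on MV if they have not reached the goal", the goals being SpO2 values at 5 and 10 minutes together with a heart rate condition. For the unit: "In the NICU, infants will be started on MV when the pH is <7.20", followed by further blood gas, FiO2 and apnea conditions. Death is not mentioned.
- **Aims.** The only intubation excluded from the endpoint is the transient one for giving surfactant.
- **Secondary outcome measures.** Death is item 9, and death or severe BPD is item 10. Neither is tied to 72 hours, and no composite pairs death with MV.
- **Statistical analysis.** The primary efficacy analysis is by intention to treat. An interim analysis is planned at 100 infants.
- **SLI maneuver.** Infants whose heart rate stays low go to resuscitation under an external guideline, and control infants are also assisted under such a guideline. The section then says: "All enrolled infants will be transferred to the NICU in NCPAP".

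**The concern.** Death within 72 hours ends the chance of needing MV. A rule with two categories, neither of which mentions death, puts an infant who dies without needing MV on the success side. If such deaths were more frequent in one arm, that arm would look better on the primary endpoint because of them. Infants of 25 to 28 weeks at high risk of RDS are a population in which early death has to be provided for, and the trial is unblinded, so the scoring rule should leave little to interpretation.

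A related difficulty affects infants with a poor course in the first minutes. Need for MV is defined by the start criteria, and those for the delivery room are SpO2 goals first checked at 5 minutes. An infant ventilated during resuscitation before that check meets none of them, so the text does not settle how that infant is scored.

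**Working it through.** **1. How the rule classifies early deaths**

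| Infant within 72 hours | Score under the text |
|---|---|
| MV started, then death | Failure |
| Start criterion met, death before MV began | Can be read as failure, since the rule scores need; not stated |
| No criterion met or recorded, no MV, death | Success |

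Only the third row is scored wrongly by the rule as it stands. Intention to treat keeps that infant in the denominator.

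**2. The plan's own figure**

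Inputs from the Sample size section: 35% versus 20%, 80% power, level 0.05. The sidedness is not stated; two-sided is taken here because it reproduces the figure.

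n = [z(0.975)·√(2p̄(1−p̄)) + z(0.80)·√(p₁(1−p₁)+p₂(1−p₂))]² / (p₁−p₂)², with p̄ = 0.275

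n = [1.960 × 0.6315 + 0.8416 × 0.6225]² / 0.15² = 3.103 / 0.0225 = 137.9, so 138 per arm. This matches the plan.

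**3. Effect on a single result**

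Uncorrected chi-square, 138 per arm: χ² = [(a−b)/138]² / [p̄(1−p̄)·2/138], with p̄ = (a+b)/276. One infant is 1/138 = 0.7 percentage points.

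| Control failures | SLI failures | Situation | P |
|---|---|---|---|
| 48 | 33 | last significant SLI count with 48 control failures | 0.047 |
| 48 | 34 | one SLI death rescored as failure | 0.065 |
| 48 | 35 | two SLI deaths rescored | 0.088 |
| 49 | 34 | one death rescored in each arm | 0.049 |
| 48 | 28 | approximately the design rates | 0.007 |
| 48 | 29 | design rates, one SLI death rescored | 0.011 |
| 48 | 30 | design rates, two SLI deaths rescored | 0.016 |
| 48 | 31 | design rates, three SLI deaths rescored | 0.024 |

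**4. Effect on error rates if such deaths fall in one arm only**

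Assume that failure by MV or death is 35% in both arms, and that a fraction d of SLI infants fail only by death without MV. The MV-only comparison is then 35% versus 35% − d. The chance of a significant result favouring SLI is

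Φ{[d√138 − 1.960·√(2p̄(1−p̄))] / √(p₁(1−p₁)+p₂(1−p₂))}

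- d = 2%: 35% versus 33%, RR 0.94, chance 5.4%.
- d = 5%: 35% versus 30%, RR 0.86; Φ[(0.587 − 1.298)/0.661] = Φ(−1.07), chance 14.1%.

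The nominal chance in that direction is 2.5%. The values of d are assumptions; the document gives none.

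**5. Power if such deaths are counted as failures**

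MV rates are held at 35% and 20%, with assumed rates of death without MV equal in the two arms.

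| Deaths without MV, each arm | Rates compared | Power at 138 per arm | n per arm for 80% |
|---|---|---|---|
| 0% | 35% vs 20% | 80.0% | 138 |
| 1% | 36% vs 21% | 79.1% | 141 |
| 2% | 37% vs 22% | 78.3% | 144 |
| 5% | 40% vs 25% | 76.1% | 152 |

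If the deaths fall in the SLI arm only, power falls further: 66.9% for 35% versus 22%, and 44.1% for 35% versus 25%. That drop is not a cost of the rule. It reflects a smaller true benefit, which MV alone would hide.

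**The case against.** The endpoint was chosen for a stated reason, comparability with an earlier trial. Mortality is recorded for every infant, death is a secondary outcome and serious adverse events are reviewed, so an excess of deaths would be seen. The handling of deaths before the event is often left to a full protocol or analysis plan, and neither is shown. This has weight for the choice of endpoint. It does not answer the scoring point, because the success and failure rule is fixed in this text and gives the wrong score for one class of infant. Reporting death separately would reveal an imbalance without correcting the primary result.

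A reader might infer that early deaths in general improve an arm's result. The text does not support that. Deaths after MV began are failures, and an infant who met a start criterion before dying can be read as a failure, because the rule scores need and not receipt.

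A reader might also infer that a handful of deaths would overturn the trial's conclusion. That holds only at the boundary of significance and with the deaths in one arm. One death in each arm leaves the borderline case just significant (P=0.049), and at the design rates three SLI-only deaths leave P=0.024.

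Finally, the sentence on transfer in NCPAP may be meant as the usual route, and the Aims section, which excludes only intubation for surfactant, suggests that other MV counts. Both are plausible readings, but the text does not settle them.

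**Conclusion.** The concern holds in a limited form. An infant who dies within 72 hours without MV and without having met a start criterion is scored a success, and such deaths lower that arm's failure rate. The number of infants affected is unknown, because the document gives no rate. The effect is negligible if these deaths are rare and balanced, and material if they differ by arm or the result is close to the threshold. Nothing in the document indicates that SLI causes such deaths; the scenarios with deaths in the SLI arm only show what the rule would conceal if it did.

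Separately, the Aims, Primary outcome measure, SLI maneuver and Criteria for starting MV sections do not agree on what counts. They leave open whether MV begun during delivery-room resuscitation is a failure, and whether meeting the criteria or receiving MV decides the score. The statement that every enrolled infant is transferred in NCPAP conflicts with starting MV in the delivery room. These points call for reconciliation. They do not justify replacing the criteria with MV for any reason, because the protocol relies on strict criteria and definitions to limit bias in an unblinded trial.

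**What to change.** Before any comparison by arm, including the interim analysis at 100 infants:

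1. State in the Primary outcome measure section that death within 72 hours without MV counts as failure, and report MV alone alongside for comparability with the earlier trial. At minimum, prespecify a sensitivity analysis of the primary endpoint with such deaths counted as failures.
2. For endpoint scoring, reconcile the four sections named above, so that it is clear whether MV begun during delivery-room resuscitation counts, and whether meeting the criteria or receiving MV is decisive. This concerns scoring only; no clinical rule needs to be chosen here.

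Cost: mortality is already collected, though the date of death and the time of starting MV must be precise enough to apply the 72-hour limit. The endpoint would differ slightly from the earlier trial's. The trial is already recruiting, so the change needs a documented amendment made without knowledge of outcomes by arm. With balanced deaths of 1% to 5% (assumed), power at 138 per arm falls from 80% to about 79% to 76%, and restoring 80% would take 141 to 152 per arm. The sensitivity analysis alone changes neither the endpoint nor the sample size, but it leaves the primary result scored as it is now.

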### Secondary outcome measures

1. Need for conventional or high frequency modes of ventilation in the first 3 hours of life.

2. Highest FiO_2_ and oxygentherapy duration.

3. Duration of NCPAP, need and duration of bi-level nasal continuous positive airway pressure (BiPAP) and NIMV.

4. Need and duration of conventional MV (synchronized intermittent mechanical ventilation (SIMV), synchronized intermittent positive pressure ventilation (SIPPV), pressure support ventilation (PSV) with or without with volume guarantee (VG)) or high frequency ventilation (HFV).

5. Duration of hospitalization.

6. Highest mean airway pressure (MAP) during MV.

7. Need and number of doses of surfactant.

8. Occurrence of mild, moderate and severe bronchopulmonary dysplasia (BPD) [10].

9. Death.

10. Death or severe BPD.

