### Sample size

We hypothesize that SLI maneuver might decrease the need for MV during the first 72 hours of life from 35% to 20%. We calculated that 138 newborns must be enrolled in each group to detect this difference as statistically significant with 80% power at a level of 0.05.

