### Randomization

Infants at each unit will be assigned to a block (1st block: gestational age from 25^+0^ to 26^+6^ weeks; 2nd block: gestational age from 27^+0^ to 28^+6^ weeks) and randomly assigned to a treatment group in 1:1 ratio using automatically generated sealed opaque envelopes, which will be prepared at Careggi University Hospital, Florence, Italy, and then distributed to participating centers. Block size will be concealed to investigators to ensure treatment balance between the two arms of the study.

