### Statistical analysis

The primary efficacy analysis will be conducted on an intention-to-treat basis. Clinical characteristics of infants in the SLI and control groups will be described using mean values and SD, median value and range, or rate and percentage. Univariate statistical analysis will be performed using the Student’st-test for parametric continuous variables, the Wilcoxon rank-sum test for non-parametric continuous variables and the chi-square test for categorical variables. A *P*<0.05 will be considered statistically significant. SLI treatment and clinical characteristics which are most likely associated with the need for MV (gestational age, birth weight, antenatal steroids, CRIB score, INSURE procedure and hospital of birth) will be included in multiple logistic regression analysis to assess their independent role in predicting SLI success or failure. Effect estimates will be expressed as relative risk (RR) with profile likelihood-based 95% confidence limits.

An interim analysis is planned when 100 infants are enrolled (50 in each arm).

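### Highest MAP exists only for ventilated infants, a group that SLI is meant to shrink, so the planned between-arm test of it does not compare randomised groups

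*Protocol article*

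**What the plan says.** All references are to the protocol article.

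- **Secondary outcome measures**, item 6: "Highest mean airway pressure (MAP) during MV". Item 4 covers the need for and duration of conventional or high-frequency ventilation.
- **Primary outcome measure**: "The primary endpoint of this study will be the need for MV within the first 72 hours of life".
- **Sample size**: the hypothesised fall is from 35% to 20%, and "138 newborns must be enrolled in each group" to find it "statistically significant with 80% power at a level of 0.05".
- **Criteria for starting MV**: ventilation begins on oxygen saturation targets in the delivery room and, in the NICU, on blood-gas or apnea thresholds.
- **Statistical analysis**: continuous variables are compared by Student's t-test or by "the Wilcoxon rank-sum test for non-parametric continuous variables". Intention-to-treat is stated for the primary efficacy analysis. Nothing is said about infants who have no MAP value, and nothing limits item 6 to description.

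**The concern.** The restriction to time on MV is part of the outcome's definition, so the comparison can include only infants who were ventilated. Whether an infant is ventilated is the very thing SLI is meant to change. If SLI works, fewer SLI infants enter the comparison, and those who do need not resemble the ventilated controls. Suppose the infants spared are mainly the milder ones. The SLI infants still ventilated are then the sicker remainder, and their peak pressures can be higher on average although SLI raised nobody's pressure.

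This does not depend on deaths. At stake is a secondary result that could point against the primary one. The Background section gives ventilator-induced lung injury a large part in BPD, so a reader could take a higher MAP under SLI as a sign of harm.

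**Working it through.** **1. The plan's own figure.** Inputs from Sample size: 35% and 20%, power 80%, level 0.05 (taken as two-sided). With a pooled variance under the null, mean rate 0.275 and no continuity correction:

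n = [1.960 × √(2 × 0.275 × 0.725) + 0.842 × √(0.35 × 0.65 + 0.20 × 0.80)]² / 0.15² = 137.9, so 138 per group.

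The stated 138 is reproduced, with power 0.800.

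**2. Who has a MAP value.** Control: 138 × 0.35 = 48.3. SLI: 138 × 0.20 = 27.6. Together that is 75.9 of 276, or 27.5%. These are 72-hour rates, while item 6 has no 72-hour limit, so the counts are rough.

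**3. Shift in the mean.** Assume SLI causes no infant to be ventilated and changes no infant's MAP. Then 20% of infants are ventilated under either arm, with mean MAP A, and 15% are ventilated only under control, with mean A − g.

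- SLI mean = A
- Control mean = [0.20A + 0.15(A − g)] / 0.35 = A − (0.15/0.35)g
- Apparent excess with SLI = 0.43g

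The protocol does not give g. For assumed gaps of 0.5, 1, 2 and 3 cmH2O, the excess is 0.21, 0.43, 0.86 and 1.29 cmH2O.

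**4. The same shift from a severity model.** Let severity be standard normal, with the top 35% ventilated under control and the top 20% under SLI. Let MAP have correlation ρ with severity. Mean severity above a cut-off that leaves a fraction p is φ(z)/p.

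- Top 35%: 0.370/0.35 = 1.058
- Top 20%: 0.280/0.20 = 1.400
- Spurious difference = ρ × (1.400 − 1.058) = 0.342ρ SD of MAP

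This is 0.10, 0.17, 0.24 and 0.34 SD at ρ = 0.3, 0.5, 0.7 and 1, and zero at ρ = 0.

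**5. How often the test would mislead.** Simulated trials had 138 infants per arm, MV rates of 35% and 20%, no effect of SLI on any infant's MAP, and a rank-sum test among ventilated infants. Two unknowns were varied: ρ, and the share of avoided ventilation that falls among the milder would-be ventilated infants (65th to 80th severity percentile). Entries are the percentage of trials significantly worse with SLI. Ranges are over repeated runs.

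| ρ | 100% of avoided MV among milder | 75% | 60% |
|---|---|---|---|
| 1 | about 90 | 39–42 | about 15 |
| 0.7 | 21–23 | 8–10 | 5–6 |
| 0.5 | 11–12 | 6–7 | 4 |
| 0.3 | 6–7 | 3–4 | 3 |

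The milder band holds 0.15/0.35 = 43% of the would-be ventilated. If 43% of the avoided ventilation falls there, sparing is unrelated to severity, and the rate is about 2% to 3% even at ρ = 1. That matches the 2.5% expected by chance in one direction. A t-test in the 100% column gave similar results: 5.9%, 12.4% and 22.2% at ρ = 0.3, 0.5 and 0.7. In those t-test runs the estimate pointed against SLI in 67%, 78% and 89% of trials.

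**6. An all-infant rank test.** With never-ventilated infants ranked lowest, the test significantly favoured SLI in about 60% to 80% of trials over the same settings, although no infant's MAP had changed. It mostly detects the difference in MV rate.

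**The case against.** The strongest reply is that the size of the problem is unknown and may be small. The protocol gives no link between severity and MAP and does not say that SLI spares the milder infants. Ventilation can start for several reasons, and apnea is a poor guide to the airway pressure an infant will later need, so a correlation near 1 is implausible. If sparing is random or the correlation is zero, the bias vanishes. All of this stands, and it limits the size. It does not make the ventilated subsets randomised groups.

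A second reply is that an analysis plan, not shown, may settle how infants without a value are handled. It could repair the point. But the article itself restricts the outcome to time on MV and names a two-group test, so the difficulty lies in the printed definition.

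Three stronger readings are tempting, and the documents do not support them.

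- A reader might infer that a working SLI will look harmful on MAP in about nine trials in ten. That figure needs severity and MAP to be perfectly correlated and every avoided ventilation to be among the milder infants.
- A reader might infer that MAP is the trial's main safety measure. The Safety section defines safety through serious adverse events and does not name MAP, which is one of ten secondary outcomes.
- A reader might infer that duration of MV is already affected. It is affected only if it is summarised among ventilated infants, and zero is a natural value for the rest.

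**Conclusion.** The point holds. As defined, item 6 can be compared only between groups selected after randomisation by the event SLI is meant to prevent, so a difference in either direction cannot be read as an effect of SLI on airway pressure.

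The harmful direction needs two things that the protocol does not quantify: SLI sparing mainly milder infants, and MAP rising with severity. With all avoided MV among the milder infants and assumed correlations of 0.3 to 0.7, a false significant result against SLI arises in about 6% to 23% of trials, and in fewer if sparing is less selective. The fault concerns one secondary outcome. It leaves the primary endpoint and the sample size untouched.

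**What to change.** - Report highest MAP among ventilated infants, with the number ventilated in each arm, as description only: no P value and no treatment claim.
- State that duration of MV is analysed in all randomised infants, counting never-ventilated infants as zero.
- If an all-infant rank analysis of MAP is wanted, with never-ventilated infants lowest, make it optional and label it a composite that largely reflects the MV rate. It is not a test of airway pressure.

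The change takes a sentence or two in the outcome definitions and needs no new data. The cost is that one secondary outcome loses its between-arm test.
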